#### Stroke and TIA

All occurrences of stroke and TIA occurring from the time of randomisation will be obtained from medical records and reported by site staff in the study database. For each event (stroke and TIA), the total number of events and the total number of patients affected will be calculated for each treatment group. The number of events reported per participant will also be calculated. Crude rates will be calculated for each outcome measure as described above for recurrent MIs.

#### Hospitalisation for heart failure

All hospitalisations for heart failure occurring from the time of randomisation will be obtained from medical records and reported by site staff in the study database. The total number of events and the total number of patients affected will be calculated for each treatment group. The number of events reported per participant will also be calculated. A crude rate will be calculated in each treatment group as described above for recurrent MIs.

### Bleeding

All bleeding events occurring from the time of randomisation will be reported if they are Type 2 or higher according to the BARC definition.

Time to first BARC Type 2 or higher event will be explored, as per the request of the DMC [at their meeting on 4th September 2018]. This will be measured as the time from randomisation to date of first BARC Type 2 event. Patients who are event-free at the time of analysis will be censored at the date they were last seen or assessed, or their date of death.

The total number of bleeding events, and the total number of patients affected, will be calculated for each treatment group. The number of events reported per patient will also be calculated. A crude rate of bleeding events [Type 2 or higher] will be calculated as described above.

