#### Recurrent MI, coronary angiography, coronary revascularisation, stroke, TIA, hospitalisation for heart failure

For each outcome measure, the number of participants reporting the event, the number of events per participant, and the total number of events (including multiple events per participant) will be tabulated by randomised group. The crude rate (total number of events or total follow up time) will also be reported alongside 95% CIs.

Time to non-fatal MI, time to first (non-trial) coronary angiography and time to first (non-trial) revascularisation will be estimated using Kaplan-Meier methods. Estimates of the treatment effect (HR) will be made using Cox regression models, as described above and reported with 95% CI's. The proportional hazards assumption will be assessed, and alternatives explored as previously described. Competing risks analyses will also be performed with death as the competing event, as per section 5.1.3.

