### Bleeding

The number of participants reporting a bleeding event, the number of events per participant, and the total number of events (including multiple events per participant) will be tabulated by randomised group. The crude rate (total number of events or total follow up time) will also be reported alongside 95% CIs. Data will also be summarised descriptively by BARC type/grade. A Kaplan-Meier plot will be used to show time to first bleed (BARC  $\geq 2$ ) by randomised group.

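### The SAP dates the bleeding outcome by the first BARC Type 2 event, not Type 2 or higher, and plans only a Kaplan-Meier curve for it despite censoring at death

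*Supplement*

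**What the plan says.** SAP v2.0, section 2.4 Bleeding, sets the scope first: "All bleeding events occurring from the time of randomisation will be reported if they are Type 2 or higher according to the BARC definition". It then introduces the time-to-event version: "Time to first BARC Type 2 or higher event will be explored, as per the request of the DMC". The next sentence says how that time is obtained: "This will be measured as the time from randomisation to date of first BARC Type 2 event". By the censoring rule that follows, anyone without an event leaves the risk set when last seen or assessed, or on dying. The section closes with the rate: "A crude rate of bleeding events [Type 2 or higher] will be calculated as described above".

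Section 5.2 Bleeding gives the analysis: "A Kaplan-Meier plot will be used to show time to first bleed (BARC", with a threshold of 2 or above completing the phrase. The example table of primary and secondary time-to-event outcomes in 5.2 has a bleeding row at BARC 2 or above with a hazard ratio. Its footnote restricts p-values to the primary outcome.

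For time to non-fatal MI, non-trial angiography and non-trial revascularisation, section 5.2 goes further: "Competing risks analyses will also be performed with death as the competing event".

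**The concern.** There are two separate matters.

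The first is wording. Section 2.4 is where outcomes are derived, and its dating sentence omits the words that extend the event above Type 2. If that sentence alone drove the program:
- a patient with a Type 3a bleed early and a Type 2 bleed months later would be timed at the later bleed;
- a patient whose only bleed was Type 3b would have no event date;
- a fatal Type 5 bleed would fall on or near a date that the next sentence names as a censoring date.

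The bleeds lost would be the severe ones. Type 4 bleeds are CABG-related and CABG is part of the invasive strategy, so a literal rule could also lose more events in that arm.

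The second is the estimator. Bleeding is a principal harm to weigh against any benefit of the invasive strategy, and readers will take absolute risk from the plotted curve. When deaths are censored, one minus Kaplan-Meier estimates the risk of bleeding as if nobody died of anything else. In patients aged 75 and over after an NSTEMI, that exceeds the proportion who actually bleed.

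**Working it through.** **1. The event definition, statement by statement.**

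| Place | Event |
|---|---|
| Protocol v3.0, 2.3.2 | BARC 2 or above |
| SAP v2.0, 2.4 Bleeding, capture rule | Type 2 or higher |
| SAP v2.0, 2.4 Bleeding, outcome name | Type 2 or higher |
| SAP v2.0, 2.4 Bleeding, **date rule** | **Type 2** |
| SAP v2.0, 2.4 Bleeding, crude rate | Type 2 or higher |
| SAP v2.0, 5.2, time-to-event table | BARC 2 or above |
| SAP v2.0, 5.2, table of event counts | BARC 2 or above, broken down from Type 2 to Type 5b |
| SAP v2.0, 5.2 Bleeding, plot | BARC 2 or above |

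One statement in eight departs from the rest. It cannot be read as shorthand, because the BARC table in protocol v3.0 (appendix 16.5) defines Type 2 as bleeding that fails the criteria for Types 3, 4 and 5.

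**2. Size under a literal reading.** Let s be the share of bleeders whose first qualifying bleed is Type 3 to 5, and r the share of those who later have a Type 2 bleed. Then:
- s × r of bleeders are timed late;
- s × (1 − r) have no event date.

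The documents give neither s nor r. If s is assumed to be 10 to 50% and r is 0, then 10 to 50% of first bleeds are lost. That range only restates the assumption. With the missing words restored, the loss is zero.

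**3. Censoring at death.** The documents give no bleeding rate and no death hazard for this cohort, so both are assumed, constant over time: bleeding b = 0.04 to 0.06 per year, death without a prior bleed d = 0.10 to 0.15 per year. The horizon is t = 5 years, the maximum follow-up.

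- One minus Kaplan-Meier, deaths censored: 1 − exp(−b t)
- Cumulative incidence: b/(b + d) × [1 − exp(−(b + d) t)]

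| b | d | 1 − KM | Cumulative incidence | Ratio |
|---|---|---|---|---|
| 0.04 | 0.10 | 1 − exp(−0.20) = 18.1% | 0.2857 × 0.5034 = 14.4% | 1.26 |
| 0.04 | 0.15 | 18.1% | 0.2105 × 0.6133 = 12.9% | 1.40 |
| 0.06 | 0.10 | 1 − exp(−0.30) = 25.9% | 0.3750 × 0.5507 = 20.7% | 1.26 |
| 0.06 | 0.15 | 25.9% | 0.2857 × 0.6501 = 18.6% | 1.40 |

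The curve is too high by 3.7 to 7.3 percentage points, or about 26 to 40% in relative terms. A higher death hazard widens the gap.

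**The case against.** The strongest reply on wording is that the plan leaves no real doubt. The disputed sentence refers back to the outcome just named as Type 2 or higher, and every other statement agrees. A programmer working from section 5.2 and the tables would code 2 or above. This stands, and it is why the point is one of drafting.

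A reader might infer that the plan excludes major and fatal bleeds, or that such patients are to be censored as bleed-free. The documents do not support either. The date rule does not say that only Type 2 counts. Censoring applies to patients who are event-free, and a patient with a Type 3 to 5 bleed is not event-free under the outcome's own name. Numbers of patients, numbers of events and crude rates are also reported by arm and by BARC type without using the date rule, so severe bleeds will be visible on any reading.

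On competing risks, the text after the time-to-event example figure in 5.2 promises tables and figures of cumulative incidence and sub-hazard ratios. That might be meant to include bleeding. It is general, however, and neither bleeding section mentions it, whereas non-fatal MI and the procedures are named explicitly. A reader might also infer that the bleeding hazard ratio is invalid. It is not: censoring at death gives a legitimate cause-specific hazard ratio. The overstatement concerns the height of the curve.

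**Conclusion.** The inconsistency is real and is in the current SAP. It is most likely a slip, and its effect on results depends on someone coding one sentence against the rest of the plan. No expected loss of events can be quoted, because the documents give no share of Type 3 to 5 first bleeds.

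The competing-risk point is a worthwhile improvement. Its size, 18 to 26% plotted against 13 to 21% actual at five years, rests wholly on the assumed constant hazards and is illustrative.

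Both parts are minor. The outcome is secondary, is described as exploratory, was requested by the data monitoring committee and has no p-value. They still merit correction, because a derivation rule should not leave the programmer to choose between adjacent sentences, and the absolute bleeding risk in each arm is a figure that readers will use.

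**What to change.** In SAP section 2.4 Bleeding, make the end point of the clock the date of the first BARC Type 2 or higher event, and list the types: 2, 3a to 3c, 4, 5a and 5b.

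In section 5.2 Bleeding, add a sentence stating that Aalen-Johansen cumulative incidence will be shown by arm, with death as the competing event and fatal bleeds counted as bleeding events. This matches what 5.2 already plans for non-fatal MI, angiography and revascularisation. The cause-specific hazard ratio in the time-to-event table can stay.

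The cost is one phrase and one sentence. No new data are needed, and the methods are already in the plan.

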### Procedural and in-hospital complications

Serious adverse events which are causally (possible, probable or definitely) related to the study angiography or PCI will be reported in patients randomised to the invasive arm undergoing their allocated coronary angiography procedure. Complications related to CABG will not be reported.

Expected procedure related complications include:

- Death
- Myocardial Infarction
- Minor (BARC<2) and major bleeding (BARC≥2)
- >25% increase in serum creatinine concentration from baseline
- Need for renal replacement therapy
- Coronary Dissection
- Aortic Dissection
- Coronary perforation
- Stroke
- TIA
- Cardiac tamponade
- Emergency repeat angiography or PCI procedure
- Procedure related pulmonary oedema
- Vascular complications needing intervention.

### Frailty score

Frailty will be assessed using Fried and Rockwood scores at index hospitalisation, at 6 and 12 months after randomisation and annually up to 5 years. Scores at each time point will be calculated at site according to the developers' instructions, taking values 0-5 (Fried) and 1-7 (Rockwood).

Fried scores will be categorised as

- Frail (score ≥3)
- Non-frail (score <3).

and

- Robust (score=0)
- Pre-frail (score=1, 2)
- Frail (score ≥3)

Similarly, Rockwood scores may be categorised as

- Frail (Rockwood score  $\geq 5$ )
- Non-frail (Rockwood score  $< 5$ ).

Change from baseline to each follow-up time-point will be calculated as the follow-up score minus the baseline score. Changes in status from baseline will be defined as transitions between frail and non-frail states (i.e. Stable (non-frail): non-frail to non-frail, Stable (frail): frail to frail, Worsening: non-frail to frail, Improving: frail to non-frail).

#### Length of time spent at home

At index hospitalisation, 6 months and 12 months after randomisation and annually up to 5 years, participants are asked to complete a resource use questionnaire which asks the main place they have lived in the last 6 months:

- In their own home
- A relative or friend's home
- Sheltered housing
- Residential home
- Nursing home.

Length of time spent at home will be defined as the time from trial entry to first report of living in a residential or nursing home. The exact date will not be known so will be taken as the date at which the questionnaire was completed. Patients not known to be living in a residential or nursing home will be censored using the date of the last completed resource use questionnaire.

## 2.5 Sample size and power

### Original calculation

The original recruitment target for this trial was a total of 2300 patients (1150 in each arm).

In previous studies, the all-cause death rates in frail and non-frail patients presenting with NSTEMI was approximately 30% at one year, which equates to an assumed 12-month 'event-free survival' rate on the conservative therapy arm of 70% at 12-months. In our trial, the estimated reduction in event rate due to including only cardiovascular (CV) deaths was anticipated to be counter balanced by an increase in event rate due to the inclusion of non-fatal MI.

A clinically relevant effect size is assumed to be a 20% reduction in the overall event rate. To detect a clinically relevant reduction in CV death and MI from 30% to 24% at 12-months equates to a clinically relevant increase in event-free survival from 70% to 76% and a Hazard Ratio (HR) = 0.77. Standard sample size formula for a log-rank test requires 620 events to be observed to detect a HR of 0.77 with 90% power and two-sided type I error of 5%. To observe 620 events with 12 month follow-up would require  $620/(0.3+0.24) = 1149$  patients to be recruited to each group. The original recruitment target was therefore 2300 patients (1150 in each group).

### Updated sample size calculation

In late 2018, an assessment of study progress was made by the trial management group and the trial steering committee. It was accepted that recruitment was at a much slower rate than originally projected and the study would require a considerable extension to recruitment in order to reach the target sample size of 2300. Furthermore, a blind review of available primary outcome data (unadjudicated) to December 2018 suggested the probability of an event in the first year (aggregated across treatment groups) was lower than originally anticipated at approximately 20%.

The original sample size calculation effectively assumes patients are only followed-up for 12 months. However, in reality, patients are followed up throughout the trial, not just to 12 months, and the analysis will make use of all data available on all patients. This allows events to accrue over a longer period, so fewer patients would need to be recruited to achieve the required number of events.

A more realistic approach to sample size estimation, as detailed in Barthel *et al.*, 2006, allows events beyond one-year to be incorporated by assuming the event rate follows a piecewise exponential distribution; the recruitment rate across the trial can also be taken into account as this will inform the duration of follow up available for each patient at the time of the primary analysis. This approach can be implemented using the Stata function ARTSURV (version 1.1.0).

Assuming an event rate of 20% in the conservative therapy arm at 12 months and maintaining the original clinically relevant effect size of a 20% reduction equates to an event rate of 16% in the invasive therapy arm and a HR of 0.78. To detect a HR of 0.78 with 90% power and 5% two-sided type I error requires around 700 events to be observed.

If the original recruitment period is extended for 24 months (i.e. a total recruitment period of 5 years) and a recruitment rate of 32 patients/month can be maintained then the study will recruit 1668 patients and have 92.5% power (5% two-sided type I error) to observe a HR of 0.78 assuming an event rate in the control group of 20% with the analysis taking place 1 year after the last patient is recruited and utilising all available follow-up data. This assumes a total of 752 events will have occurred at the time of the primary analysis. While this sample size gives a power higher than that for the original sample size calculation (90%), it will offer some protection against non-proportional hazards, treatment crossover, loss to follow-up and competing risks (non-CV deaths).

The table below gives the power (and expected number of observed events) under various recruitment and minimum follow-up scenarios.

**Table: Power (and expected number of events [E]) under various recruitment and follow-up scenarios (assuming a 20% control group event rate at 1 year and HR=0.78)**

|                                                                  | 12-month recruitment extension (total recruitment period of 4 years) |                   |                   | 24-month recruitment extension (total recruitment period of 5 years) |                   |                   |
|------------------------------------------------------------------|----------------------------------------------------------------------|-------------------|-------------------|----------------------------------------------------------------------|-------------------|-------------------|
| Monthly accrual for remaining trial duration (from Jan 19)       | 28p/m                                                                | 30p/m             | 32p/m             | 28p/m                                                                | 30p/m             | 32p/m             |
| Expected sample size achieved                                    | 1204 a                                                    | 1244 b | 1284 c | 1540 d                                                    | 1604 e | 1668 f |
| Follow-up for at least 1 year after last patient entered  | 0.784
(E=491)                                                     | 0.795
(E=505)  | 0.804
(E=516)  | 0.909
(E=705)                                                     | 0.919
(E=732)  | 0.925
(E=752)  |
| Follow-up for at least 2 years after last patient entered | 0.87
(E=619)                                                      | 0.879
(E=637)  | 0.887
(E=654)  | 0.952
(E=854)                                                     | 0.959
(E=888)  | 0.964
(E=915)  |

Proportion of target sample size recruited per year:

a (10%; 33%; 29%; 28%)

b (10%; 32%; 29%; 29%)

c (10%; 30%; 30%; 30%)

d (8%; 26%; 22%; 22%; 22%)

e (8%; 25%; 23%; 22%; 22%)

f (7%; 24%; 23%; 23%; 23%)

The calculations outlined above assume the treatment effect (HR=0.78) persists over time. In this patient population, it may be unrealistic to expect this to be the case and if the treatment effect diminishes over time then this would potentially lead to an under-powered study. An alternative assumption, which serves as a sensitivity analysis to assess the likely effect of a diminishing treatment effect, is to assume that the hazard ratio of 0.78 persists for the first two years after randomisation, but that it is attenuated thereafter to a value intermediate between 0.78 and 1 (see below **figure**). For example, if the HR increased to 0.90 after 2 years, the power reduces to 80% (assuming an event rate of 20% in the control group, a total sample size of 1668 patients and an analysis that takes place 1 year after the last patient is recruited and utilises all available follow-up data).

**Figure: Power allowing for non-proportional hazards**[figure not shown]

In the event that recruitment cannot be maintained at 32 patients/month, alternative strategies could be employed, such as further reducing the sample size and extending the minimum follow-up to 2 years (see above **table**).

## 3. STATISTICAL CONSIDERATIONS

### 3.1 Timing of analyses

The primary analysis is scheduled to take place once all participants have been followed-up for one year and will make use of all available follow-up data. The number of primary endpoint events, both overall and by arm, will be monitored periodically by the independent data monitoring committee (DMC) against the target number. The achieved power based on the final sample size and observed number of events will be calculated for information.

### 3.2 Interim analyses, data monitoring and stopping guidelines

The trial will be monitored by an independent data monitoring committee (DMC) that will meet at the start of the trial and at least annually thereafter, unless otherwise agreed. The DMC will review data summaries corresponding to the specific roles described in the DMC charter; e.g. recruitment, data quality, adherence to protocol treatment and follow-up and descriptive summaries of safety data and main efficacy outcome measures. Underlying assumptions pertaining to the sample size calculations, including overall numbers of CV deaths and non-fatal MI, will be monitored by the DMC. The DMC will not be blind to treatment allocation.

Accumulating patient data will be reported to the DMC but (in addition to any summaries performed at the requested of the DMC) interim analyses of primary outcome data will not be undertaken until 50% of patients are recruited. While there are no formal stopping rules proposed for this trial, the DMC will make recommendations to the TSC as to whether to stop or continue recruitment based on all available evidence: when interpreting significance levels attention will be paid to Peto-Haybittle boundaries.

### 3.3 Analysis populations

**Intention to treat (ITT):** This population contains all patients randomised into the study (regardless of whether they were later found to be ineligible, a protocol violator, not receiving the allocated treatment etc.).

**Safety population:** This population contains patients in the intervention group undergoing their randomised coronary angiography.

Analysis of the primary endpoint and all secondary endpoints (apart from procedural and in-hospital complications) will be conducted in the ITT population. Procedural and in-hospital complications will be presented in the safety population.

There will be some participants allocated to the invasive strategy who do not undergo their allocated procedure and some participants allocated to conservative management who go on to receive coronary angiography. However, any analysis in a per-protocol population, of participants receiving their allocated treatment strategy as per-protocol, is likely to be biased as treatment assignment would no longer be random and there would likely be an association between treatment switching and the risk of a clinical event. Furthermore, treatment switching reflects real-life clinical practice and a per-protocol analysis of participants receiving their allocated treatment as per-protocol would not estimate real-life clinical effectiveness. For these reasons, it is not planned to conduct any analyses in a per-protocol population of participants receiving their allocated treatment strategy.

A per-protocol analysis, excluding any participants found to be ineligible after randomisation, may be conducted as a sensitivity analysis if the number of ineligible patients is found to be excessive (>2.5%).

